#### Adherence Protocol

We will use the following protocol to encourage participants’ adherence to the data collection schedule. All decision points are based solely on data collection, rather than any indication of the intervention use or nonuse. The protocols for daily and weekly data collection were independently run.

*The daily measures adherence protocol* will be as follows: when a participant misses their end-of-day questionnaire, the system automatically generates a reminder next morning. If a participant has already received 2 automated reminders in a row and again misses daily measures, a research assistant will call the participant (in addition to an automated reminder) on the next workday, following a predetermined call script. If the participant does not respond, they will receive one more reminder the next day, and a second call on the following workday. If no data are received, the participant will be marked as dropped out as they will have missed at least 6 subsequent daily measures (ie, more than 20% of the overall data points). The protocol resets when the participant submits a daily questionnaire. In summary, the daily adherence protocol was as follows: 2× reminder, 1× call+reminder, 1× reminder, and 1× call+reminder, dropped from the study.

The *weekly measures adherence protocol* will be as follows: the survey links will be sent on Saturday midday, with an automated email reminder on Sunday morning. If data are missing by the end of Sunday, a research assistant will call the participant on Monday, following a predetermined call script. The participants will be sent a new link to the survey, with the possibility of submitting their response for the week by the end of Monday. We will not use adherence to weekly surveys as a decision to drop participants from the study, as weekly surveys do not collect the primary outcome.

All calls and other communications with participants will be logged by the research assistant on the web. Although the research assistant will be able to unblind the participants’ condition if necessary, we do not expect this will be needed in most of the calls.

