#### Active Control Group

When compared with a traditional noninteractive plush toy, the intervention model underpinning Purrble includes 2 possible pathways through which the effects should occur:

The first is the in-the-moment soothing support (level 1 in the logic model) that we hypothesize is driven by the interactivity of the toy. The lack of such situated down-regulation support should thus be the key difference between the intervention and an active control, that is, a noninteractive stuffed toy, leading to lower engagement over time (level 2) and a lack of impact on child ER practice (level 3).However, an alternative pathway is the ER routines (levels 2 and 3 in the logic model) that could, in principle, emerge around the intervention narrative of a physical object to use for calming down, even without the toy being interactive. In other words, if it was simply the narrative of an anxious creature in need of care (rather than the combination of the narrative together with the interactivity) that drives long-term engagement and changes in behavior, a noninteractive stuffed toy could still lead to the development of the same routines. We see this as an unlikely scenario, for example, given the prevalence of plush toys in most, if not all, households—but one that should be addressed in the study design.

For these reasons, we argue that a comparison with a nonactive control—such as waiting list or treatment-as-usual (ie, nothing)—would not allow us to distinguish the hypothesized impact on in-the-moment soothing of interactivity versus the emergence of new family routines and would also be open to unequal social desirability bias. However, from the perspective of the hypothesized logic model, it is not necessary for the active control to have exactly the same form factor as the active toy, as long as it is comparable in size, shape, and appeal. In fact, we have explicitly decided not to use deactivated Purrble units as active controls because of the increased risk of unblinding, whereby the participants search for or come across Purrble on the web (or notice the plastic enclosure with electronics inside the toy) and assume that their unit is malfunctioning.

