### Outcome Measures

The primary outcome will be a daily EMA measure of child emotion regulation capability (as reported by parents) over a period of 4 weeks. Exploratory analyses will investigate the intervention impact on secondary outcomes of child emotion regulation, collected weekly over the same 4-week period, with follow-ups at 1 month and 6 months postdeployment. See Table 1 for a summary of the outcome measures and assessment times.

**Table 1 table1:** Summary of the outcome measures and assessment times.

Outcome measure	Baseline	Deployment				Follow-up			
		Week 1	Week 2	Week 3	Week 4	1 week	2 weeks	1 month	6 months
Perceived child ER ability		Collected daily	Collected daily	Collected daily	Collected daily				
Daily parent report ecological momentary assessment (modified differential emotions scale)		Collected daily	Collected daily	Collected daily	Collected daily				
Daily parent report ecological momentary assessment (engagement)		Collected daily	Collected daily	Collected daily	Collected daily				
Daily parent report ecological momentary assessment (reaction to triggers)		Collected daily	Collected daily	Collected daily	Collected daily				
Weekly parent questionnaire (Strength and Difficulties Questionnaire)	✓	✓	✓	✓	✓			✓	✓
Weekly parent questionnaire (ER Checklist)	✓	✓	✓	✓	✓			✓	✓
Weekly parent questionnaire (Twente Engagement With eHealth Technologies Scale)		✓	✓	✓	✓			✓	✓
Weekly children questionnaire (Difficulties in ER Scale)	✓	✓	✓	✓	✓			✓	✓
Weekly children questionnaire (emotion regulation-beliefs)	✓	✓	✓	✓	✓			✓	✓
Interviews with families						✓	✓		

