#### Data Analyses

All analyses of daily EMA outcomes (the primary outcome of daily ER and secondary outcomes of engagement with the toy and mood), as well as the analyses of the weekly outcomes, will be conducted using random-effect models for longitudinal regression. These models consider the nested nature of repeated-measures data and are robust to data missingness and violations of the normality assumption. The regression models will examine the difference in the outcome as a function of the assigned condition (Purrble vs active control). The models will adjust for the baseline levels of the score on the total difficulty scale in the SDQ to decrease noise. To account for participant-to-participant variability in EMA scoring as well as in trajectories of change in EMA scores over time, we will include a random intercept and random slope for time. All analyses will be conducted on an intent-to-treat basis and will use data from all randomized participants regardless of their level of participation.

A separate model will be fitted to each outcome. Given that this is an exploratory trial, we will not formally adjust for multiple comparisons. However, we will be cautious in our conclusions about any significant findings and will interpret all results in light of all performed analyses.

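### Read literally, the daily adherence rule removes silent families from all later data collection, which sits badly with the intent-to-treat statement and creates avoidable missing data

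*Protocol article*

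**What the plan says.** The Adherence Protocol section sets out an escalation for missed end-of-day reports: two automated reminders, a call with a reminder, another reminder, then a second call. If nothing has arrived by then, "the participant will be marked as dropped out as they will have missed at least 6 subsequent daily measures", which the section equates with "more than 20% of the overall data points". Its one-line summary of the sequence finishes "call+reminder, dropped from the study". A single report restarts the count: "The protocol resets when the participant submits a daily questionnaire".

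The same section says that the daily and weekly adherence protocols ran independently of each other. On the weekly surveys it says: "We will not use adherence to weekly surveys as a decision to drop participants from the study". The reason given is that the weekly surveys do not carry the primary outcome.

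The Data Analyses section says that all analyses are by intent to treat and "will use data from all randomized participants regardless of their level of participation". It relies on random-effect models, which it describes as robust to missing data, with a separate model for each outcome and adjustment for baseline SDQ.

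**The concern.** The rule is triggered by missing outcome data, it operates after randomization, and the study team applies it. Its wording points to removal from the whole study. The sentence on weekly surveys supports that reading, because it treats dropping as one study-level decision that missed daily reports can trigger and missed weekly surveys cannot.

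Daily reporting is the heaviest demand on parents. Someone who gives it up may still answer a weekly survey or a 6-month questionnaire. If the links stop, that chance is lost by rule rather than by the family's choice.

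Random-effect models give valid estimates when missingness can be explained by the data in the model. They do not protect against families leaving for reasons linked to unobserved outcomes. Stopping collection enlarges the part of the result that rests on this assumption. If it happened more often in one arm, the randomized comparison would be affected.

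**Working it through.** **Inputs.** Daily reports over 4 weeks (Outcome Measures), so 4 × 7 = 28. Trigger of at least 6 consecutive misses (Adherence Protocol). SDQ, ERC, DERS and ER-beliefs at baseline, weeks 1 to 4, 1 month and 6 months (Table 1), so 4 + 2 = 6 post-baseline assessments. Dropout allowance of 20% (Sample Size and Power).

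**1. The plan's own figure.** 6/28 = 21.4%, which exceeds 20%; 5/28 = 17.9% would not. The stated figure is right.

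**2. When the rule bites.** Calls are made on workdays, taken here as Monday to Friday. The count runs from the first miss to the report due on the evening of the second call.

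| First miss | First call | Reminder | Second call | Missed | Share of 28 |
|---|---|---|---|---|---|
| Mon | Thu | Fri | Mon | 8 | 28.6% |
| Tue | Fri | Sat | Mon | 7 | 25.0% |
| Wed | Mon | Tue | Wed | 8 | 28.6% |
| Thu | Mon | Tue | Wed | 7 | 25.0% |
| Fri | Mon | Tue | Wed | 6 | 21.4% |
| Sat | Tue | Wed | Thu | 6 | 21.4% |
| Sun | Wed | Thu | Fri | 6 | 21.4% |

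The range is 6 to 8 misses, in agreement with the stated minimum of 6.

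**3. What is lost if removal ends all collection.**
- Silent from day 1: 28 − 6 = 22 daily reports can no longer be given (28 − 8 = 20 at the later trigger). All 6 of 6 post-baseline questionnaires are lost if the drop precedes the week-1 survey, or 5 of 6 if that survey has already gone out. Table 1 shows no baseline daily report, so this family has no primary-outcome observation at all.
- Silent from day 8: dropped on day 13 to 15, so 28 − 13 = 15 to 28 − 15 = 13 further daily reports are lost. So are up to 5 of 6 questionnaires (weeks 2 to 4, 1 month, 6 months), or 4 of 6 if the week-2 survey is already out.

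**4. What is lost if the weekly protocol continues independently.** No weekly or follow-up questionnaire. Only later daily reports are affected.

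**5. The statements side by side.** The intent-to-treat sentence governs whose data enter the analysis. The adherence rule governs when collection stops. Both can be obeyed at once, because reports made before the drop can be analysed under the assigned arm. The tension is that the analysis takes families whatever their participation, while the rule ends participation because it is low.

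**6. Which analyses are touched.** The weekly outcomes lose later time points. The mediation analysis uses ERC and SDQ change from baseline to the end of week 4, so a family dropped before then has no change score, even if it would have answered that survey. The stated primary model contains the daily scores and baseline SDQ but no post-baseline weekly scores. For the primary outcome, therefore, the direct loss is the later daily reports.

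**7. How many families.** The allowance gives 0.20 × 120 = 24, or 0.20 × 134 = 26.8 with the abstract's sample size. This covers dropout of every kind. Nothing in the document says how much of it the rule would cause.

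**The case against.** The best defence is that the drop appears in the paragraph on daily reporting, and the section says that the two protocols ran independently. On that reading a dropped family still receives its weekly and follow-up questionnaires. The article condenses a fuller protocol, which may say so. This stands as a possible reading. The summary's wording and the weekly-survey sentence point the other way, however, and staff cannot apply both.

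The rule is also not hasty: it needs several unanswered reminders and two calls, and one report resets it. Families that ignore all of this may return little more. That limits the gain from continued contact but is no reason to forgo it.

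A reader might infer more than the document supports:
- **That intent to treat is contradicted.** It is not, as step 5 shows.
- **That data are discarded.** No collected data are said to be deleted or excluded; what is at risk is data not yet collected.
- **That the loss will be unequal.** The Active Control Group section predicts lower engagement with the control toy, not less reporting by parents. The adherence decisions rest on data collection alone, and families are not told of the other condition. Imbalance is possible but not shown.
- **That the weekly scores would rescue the primary analysis.** They are not in the stated primary model.
- **That 24 or 27 families would be removed.** That is the overall dropout allowance, at most an upper guide.

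**Conclusion.** The point holds as an ambiguity in a rule that staff must apply, with an avoidable loss of data on its literal reading. The loss per family ranges from no weekly or follow-up questionnaire, if those continue independently, to 6 of 6, if a family silent from day 1 is removed before the week-1 survey. Up to 22 daily reports could also be forgone. These figures assume 28 daily reports, calls on Monday to Friday, and a count that includes the evening of the second call. The number of families and any difference between arms cannot be derived from the document. The weekly outcomes are exploratory, which limits the consequence. The correction is nearly free, so it is worth making.

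**What to change.** State in the Adherence Protocol that reaching the trigger ends daily reminder calls only. Keep sending the daily links, the weekly surveys and the 1-month and 6-month questionnaires unless the family withdraws consent. State in Data Analyses that all returned data are analysed under the assigned arm, including data that arrive after the trigger. Replace the dropped-out label with one such as EMA non-responder, and report the number and timing by arm.

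The Results section says that primary data collection finished by mid-May 2021. For that period the remedy is to report how the rule was applied, by arm, and whether the later questionnaires were still offered. Any follow-up still outstanding can be offered to these families.

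The cost is a few extra automated emails, a sentence or two of text, and one line in the participant flow.

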#### Data Analyses

All analyses of daily EMA outcomes (the primary outcome of daily ER and secondary outcomes of engagement with the toy and mood), as well as the analyses of the weekly outcomes, will be conducted using random-effect models for longitudinal regression. These models consider the nested nature of repeated-measures data and are robust to data missingness and violations of the normality assumption. The regression models will examine the difference in the outcome as a function of the assigned condition (Purrble vs active control). The models will adjust for the baseline levels of the score on the total difficulty scale in the SDQ to decrease noise. To account for participant-to-participant variability in EMA scoring as well as in trajectories of change in EMA scores over time, we will include a random intercept and random slope for time. All analyses will be conducted on an intent-to-treat basis and will use data from all randomized participants regardless of their level of participation.

A separate model will be fitted to each outcome. Given that this is an exploratory trial, we will not formally adjust for multiple comparisons. However, we will be cautious in our conclusions about any significant findings and will interpret all results in light of all performed analyses.

To examine the link between engagement with the intervention and ER outcomes, we will conduct 3 types of exploratory analyses: first, given that we hypothesize that Purrble will be more engaging than the control-condition stuffed animal, we will examine whether intervention engagement is influenced by the treatment condition. To do so, we will regress our daily measure of engagement on the treatment condition, controlling for the previous day’s engagement to reduce noise. Similarly, we will regress the weekly TWEETS scores on the treatment condition, controlling for the previous week’s engagement. Second, we will examine whether engagement moderates the intervention impact on both our primary outcome, the daily measure of emotional regulation, and the weekly ERC and SDQ measurements. For the daily model, we will use our primary measure, the EMA assessment of ER, as the dependent variable, and will include, as regressors, treatment indicators and the EMA measure of engagement, as well as a term for their interaction. To decrease noise, the model will also include as a covariate the previous day’s score on the ER measure. Similarly, for weekly models, we will regress the weekly ERC and SDQ scores on terms for the treatment indicator, TWEETS score, and their interaction. As in the daily model, we will also include a term for the ERC or SDQ score of the previous week to reduce noise. As an alternative approach, we will consider using the weekly average of the daily EMA engagement scores rather than TWEETS for the weekly analyses of the moderating influence of engagement, as these 2 scales tap into different aspects of the engagement experience.

Finally, as our logic model postulates that engagement may also mediate the impact of intervention, we will also conduct an analysis of the mediating role of engagement. Given the ambiguities of mediation analyses in longitudinal settings and the lack of consensus on best practices, for this analysis, we will follow the original Baron and Kenny approach to establishing mediation [75]. To do so, we will use, as our outcome variables, the change scores for the emotion-regulation measures (ERC and SDQ) from baseline to the end of study (end of week 4). To measure engagement, we will use the average of the weekly TWEETS assessments over the course of the study. To examine the mediating role of engagement, we will conduct 3 sets of analyses: first, we will estimate the impact of the treatment condition on the change in ER by regressing the emotion-regulation change score on the indicator of the treatment condition. Second, to examine whether treatment had an impact on engagement, we will regress the average of the weekly TWEETS assessments on the indicator for the treatment condition. Finally, we will estimate a model that regresses the ER change score on both the treatment indicator and engagement. To assess preliminary evidence on the mediating role of engagement, we will examine the magnitudes of effect coefficients in all models, as well as statistical significance, to determine whether the inclusion of engagement in the model has reduced the impact of the treatment condition. Given that the ERC and SDQ tap into different aspects of emotion regulation, we will conduct these analyses for both ERC and SDQ change scores.

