##### Secondary Hypotheses

Intervention effects will be moderated by daily engagement with toy and weekly data from the TWEETS questionnaire. In addition, we expect to see between-group differences in favor of Purrble for the secondary daily EMA parental-report outcomes: *an increase* in the *positive mDES items* and a *decrease* in the *negative mDES items*.

Finally, as exploratory analyses, we will investigate the following hypotheses for weekly outcome measures:

The decrease in *parent-reported emotional and behavioral difficulties* (as measured by the SDQ) will be greater in the intervention group (smart toy) than in the active control group (noninteractive toy).*The decrease in ER lability* and *increase in emotion regulation competence* (as measured by the Lability or Negativity subscale and Emotion Regulation subscale questionnaires respectively) will be greater in the intervention group than in the active control group (noninteractive toy).*Behavioral, cognitive, and affective engagement* with the intervention, as measured by the adapted *TWEETS questionnaire for parents*, will be higher for the intervention than the control group.The decrease in *child-reported emotion dysregulation* (as measured by the DERS) will be greater in the intervention group than in the active control group (noninteractive toy).The decrease in *child-reported entity beliefs of emotion regulation* (as measured by the ER mindset questionnaire) will be greater in the intervention group than in the active control group (noninteractive toy).

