#### Sample Size and Power

We calculated the sample size requirements to be able to detect a difference between the two arms on our primary outcome measure: the daily parent report of the child’s ER throughout the day. On the basis of the data from our preliminary studies, we expect to see a medium effect size for this measure; therefore, to be conservative, we used a Cohen *d* of 0.3 in our sample size calculation. With this assumption, we calculated the sample size to be able to detect the main effect of the condition (Purrble vs active control) with 90% power and an α level of .05. Under the conservative assumption that the correlation between repeated measures will be 0.75, the required sample size is 92 participants. We inflated this number by 10% to help power the exploratory analyses of the secondary outcomes. Assuming a 20% dropout rate, our final sample size is 120 families.

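### The daily engagement-moderation model, as written, has no between-family variation in the engagement slope, so its interaction test can be anti-conservative by an amount the protocol does not let us fix

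*Protocol article*

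**What the plan says.** Secondary Hypotheses lists engagement moderation: "Intervention effects will be moderated by daily engagement with toy and weekly data from the TWEETS questionnaire".

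Data Analyses says that all analyses of daily EMA outcomes, and the weekly ones, "will be conducted using random-effect models for longitudinal regression". To allow for differences between participants in EMA scoring and in its trajectory, "we will include a random intercept and random slope for time".

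The same section then describes the daily moderation model. The outcome is the daily ER score. The model "will include, as regressors, treatment indicators and the EMA measure of engagement, as well as a term for their interaction", and "the model will also include as a covariate the previous day’s score on the ER measure". No random slope for engagement is named.

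The moderation work is introduced with "we will conduct 3 types of exploratory analyses", and for the trial as a whole "we will not formally adjust for multiple comparisons". The protocol states no error rate for the moderation test. The only α given is the .05 in Sample Size and Power.

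**The concern.** Condition is fixed for a family and engagement changes from day to day, so condition by engagement is a cross-level interaction. The hypothesis of interest is whether the average engagement-ER slope differs between arms. A model with random effects only for intercept and time tests something narrower: equal average slopes and, in addition, no slope differences between families within an arm.

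If slopes do differ between families, the evidence on the interaction comes from about 60 family slopes per arm. The model instead treats up to 120 × 27 = 3,240 daily records (27 usable days after the one-day lag) as informing one common slope per arm. The standard error is then too small and the confidence interval too narrow. Moderation could be declared, in either direction, when the arms have the same average slope. Reading the result cautiously does not repair this, because the reader cannot tell how far the interval is too narrow.

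**Working it through.** **Inputs from the protocol.** 120 families (Sample Size and Power), allocated 1:1 (Abstract); 28 daily measures, so at most 27 with a one-day lag; correlation between repeated measures 0.75; 20% dropout; α .05, taken as two-sided. The Abstract gives 134 families rather than 120. This does not matter here, because the ratio below depends on days per family and not on the number of families.

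**Inputs that must be assumed.** The between-family SD of the engagement-ER slope, the variance split of engagement, and its autocorrelation. The protocol gives none of these.

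**Approximation.** Let s be the between-family slope SD, in residual ER SDs per within-family SD of engagement, and T the usable days per family. The ratio of true to reported variance of the interaction is about

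1 + T·s²

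and the actual rejection rate is 2[1 − Φ(1.96/√(1 + T·s²))].

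**Units.** It is easier to think of the slope SD in total ER SDs per total within-arm SD of engagement. With intraclass correlation 0.75 the residual ER SD is √0.25 = 0.5. If half the engagement variance is within family (assumed), its within-family SD is √0.5 = 0.707. So s = (0.707/0.5) × SD = 1.41 × SD.

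**Simulation in total-SD units.** True interaction zero, 60 families per arm, 28 days, previous-day ER included, 1,000 trials per cell (Monte Carlo error 0.7 to 1.4 points). Assumed: engagement autocorrelation 0.5, Purrble mean engagement 0.5 SD higher, mean slope 0.1 in both arms, time-slope SD 0.1.

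| Slope SD | s = 1.41 × SD | 1 + T·s², T = 22 to 27 | Formula | Simulated, as written | Simulated, random engagement slope added |
|---|---|---|---|---|---|
| 0 | 0 | 1 | 5.0% | 4.8% | 3.9% |
| 0.05 | 0.07 | 1.11 to 1.14 | 6.3 to 6.6% | 6.1% | 5.3% |
| 0.10 | 0.14 | 1.44 to 1.54 | 10.2 to 11.4% | 10.0% | 5.5% |
| 0.15 | 0.21 | 1.99 to 2.22 | 16.5 to 18.8% | 17.8% | 5.5% |
| 0.20 | 0.28 | 2.76 to 3.16 | 23.8 to 27.0% | 24.1% | 4.7% |

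The nominal 5% is reproduced where families share one slope. At SD 0.15 the average reported standard error is 0.027 against a true SD of 0.038; 1 − 0.027/0.038 = 29% too small. With 48 families per arm (20% dropout) the rates as written are 4.7, 6.2, 10.5, 17.4 and 26.4%. Without the lag term, at 60 per arm, they are 4.8, 6.2, 10.3, 18.1 and 24.6%.

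**Independent simulation in units of s.** 120 families, about 20% dropout, 10% missed days, baseline SDQ and lagged ER in the model, 1,000 runs per setting. As written: 5.3% (s = 0), 5.8% (0.05), 7.4% (0.10), 12.2% (0.15), 15.4% (0.20), 23.5% (0.30), 32.6% (0.40). With a random engagement slope: 5.3 to 5.8% throughout. The two sets agree once the factor 1.41 is applied. In 600-run settings where ER truly depended on the previous day (coefficient 0.3), the engagement slope was scaled down by 0.7 and inflation was lower: 9.7% at nominal s = 0.20.

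**Weekly models.** These were not simulated. The formula with T = 4 and slope SD 0.05, 0.10, 0.15 and 0.20 gives 1 + T·s² = 1.02, 1.08, 1.18 and 1.32, hence about 5.2, 5.9, 7.1 and 8.8%.

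**The case against.** The strongest reply is that this is inference from silence. The sentence on random effects does not say they are the only ones, the moderation model is described only by its regressors, the article condenses a fuller plan, and random-effects detail is often left to an SAP. A fuller plan may indeed contain the term. But the article does not leave the random part open: it covers all daily EMA analyses, names the sources of participant variability and the two random effects that handle them, and then lists the moderation terms. That is a specification that can be assessed as written.

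A reader might infer that the test runs at two to five times its nominal level. The documents do not support that as a flat statement. It requires a slope SD of about 0.10 to 0.20, which the protocol does not give. At 0.05 or below the excess is minor, and at zero there is none. SD 0.10 equals the mean slope assumed in the simulation, so about 16% of families would have a negative slope; at 0.20 it would be about 31%.

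A reader might also take the interview sampling of families with the highest or lowest change, or the daily question on how helpful the toy was, as evidence that engagement slopes differ. Neither shows it. The first concerns change in the outcome, which a random time slope can absorb. The second is an exploratory item meant to guide interviews.

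The objection also stands on stakes: the analysis is labelled exploratory, the authors promise cautious interpretation, and the Limitations section frames the secondary measures as hypothesis-generating.

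**Conclusion.** The concern holds in conditional form. As written, the daily moderation model leaves between-family variation in the engagement-ER slope out of the interaction's standard error. If such variation exists, the test is anti-conservative: about 5 to 6% for slope SD 0 to 0.05, 10% for 0.10, 18% for 0.15 and 24% for 0.20, at nominal 5%. These figures rest on the assumed slope SD, the assumed half-and-half split of engagement variance, and the protocol's correlation of 0.75. The mechanism and the correction were confirmed in two separate simulations; the size for this trial cannot be known from the protocol. More families would not cure it.

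The point is confined to an exploratory secondary hypothesis. It says nothing against the primary comparison, and it should not be extended to the weekly TWEETS models as a material problem, since four time points give only mild inflation by the formula.

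**What to change.** In the Data Analyses paragraph on engagement moderation, state that the daily model includes a by-family random slope for engagement in addition to the random intercept and random time slope. If that model does not converge, use family-clustered robust standard errors for the interaction. Robust standard errors in the weekly TWEETS moderation models are optional.

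The cost is one sentence and one variance term, with no new data. If families truly share one slope, the interaction's standard error rises from 0.0264 to 0.0272 at 60 per arm (0.0272/0.0264 = 1.03, about 3%). If they do not, the interval widens because the one given by the model as written would have been too narrow.
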